## Abstract

**Introduction::**

Antihypertensive treatment is associated with clinical outcomes in patients with spontaneous intracerebral hemorrhage (sICH). ADAPT showed that intensive blood pressure lowering (<140 mm Hg) does not reduce peri-hematoma regional cerebral blood flow (rCBF) in patients with sICH. However, the stenosis of main cerebral arteries that has a high presence in patients with sICH is well-known related to the brain ischemia. The effect of intensive BP lowering for sICH in patients with cerebrovascular stenosis is still unknown.

**Aim::**

The aim of this study was to determine the safety and effectiveness of intensive BP lowering for sICH in patients with cerebrovascular stenosis.

**Methods and analysis::**

A pilot trial has been conducted to calculate the sample size and 80 patients of sICH with cerebrovascular stenosis will be involved. The target of systolic blood pressure (SBP) will be maintained at from 120 to 140 mm Hg or from 140 to 180 mm Hg for 7 days. Cerebral ischemia will be assessed at 24 hours after onset by computed tomography (CT) perfusion imaging and the follow-up will be conducted at 30-day and 90-day. The primary outcome is the reduction of peri-hematoma rCBF. The other cerebral perfusion indexes and the rate of ischemic stroke are regarded as other primary outcomes. The secondary outcomes include clinical outcome at 30 days and 90 days, complications, and hospital stays.

**Discussion::**

The ATICHST trial has been signed as a parallel, prospective, randomized, assessor-blinded clinical trial to determine the effects of intensive BP lowering on sICH in patients with cerebrovascular stenosis, the results of which will contribute to guide the management of blood pressure in sICH.

**Conclusion::**

The protocol will determine the safety and effectiveness of intensive BP lowering for sICH with cerebrovascular stenosis.

## Background

1

Spontaneous intracerebral hemorrhage (sICH) is the second most prevalent cause of stroke, and almost 1 million patients are diagnosed with sICH every year worldwide.^[1,2]^ sICH is associated with a high rate of mortality^[3]^ and disability.^[1,4]^

Recently, the management of blood pressure (BP) has been bone of contention for the sICH patients. Almost 90%^[5,6]^ of acute sICH patients have an elevated systolic BP (SBP) caused by the elevated intracranial pressure to keep cerebral blood +flow (CBF)^[7]^ and the highest SBP always appears at 24 hours after onset.^[8,9]^ The elevated BP increases the risk of hematoma expansion,^[10]^ while the acute lowering of BP may result in the ischemia of brain tissue.^[11]^

Several high-quality, multicentric, randomized controlled trials^[12,13]^ suggested the intensive BP lowering was safety in sICH patients and the ADAPT trial showed the peri-hematoma rCBF did not decrease after intensive BP lowering.^[14]^ A meta-analysis^[15]^ including 1427 patients also suggested that intensive BP lowering was safe and might have a potency of reducing hematoma expansion and improving clinical outcome. However, all of the mentioned randomized controlled trials and related clinical studies have no subgroup to discuss sICH with cerebrovascular stenosis and the management of BP for sICH patient with cerebrovascular stenosis is still unknown.

Brain ischemia has a high incidence of 25%^[16,17]^ in patients with sICH. The hematoma is surrounded by an ischemic penumbra, which needs adequate CBF to maintain its viability.^[18]^ The intensive SBP lowering may aggravate ischemia in ischemic penumbra and results in 20% of sICH patients suffering from the brain ischemia or infarction.^[11]^

The cerebrovascular stenosis has a rate of 20% to 54%^[19]^ in sICH patients, including intracranial cerebrovascular stenosis and extracranial cerebrovascular stenosis.^[20]^ The rate of intracranial cerebrovascular stenosis (16%) was higher than extracranial cerebrovascular stenosis (6%) in Chinese.^[21]^ Many researches^[22–26]^ demonstrated that 18% to 24% of ischemic stroke was closely associated with the stenosis of main cerebral vessels. When cerebrovascular stenosis coexists with sICH, intensive SBP lowering could increase the risk of ischemia and infarction.^[20,27]^

Theoretically, the conservative antihypertensive treatment (<180 mm Hg) is safe and may be beneficial to the sICH patients with cerebrovascular stenosis. The patients undergoing conservative antihypertensive treatment may have higher peri-hematoma rCBF and lower incidence of brain ischemia or infarction, which are associated with neurological deterioration or mortality. Moreover, long-term outcome may be better for the neuroprotection after the conservative antihypertensive treatment. Thus, a well-designed clinical trial is need to assess the safety and efficacy of intensive SBP lowering for sICH with cerebrovascular stenosis, and provides powerful evidence to clinical practice. Here, we described a parallel, superiority, randomized, assessor-blinded trial termed antihypertensive treatment in patients of sICH with cerebrovascular stenosis trial (ATICHST).

## Methods

2

### Design

2.1

The ATICHST is a parallel, prospective, randomized, assessor-blinded clinical trial of intensive BP-lowering treatment and conservative BP-lowering treatment in the sICH patients with cerebrovascular stenosis, which is conducted according to the flow diagram (Fig. 1) by the Department of Neurosurgery in West China Hospital, Sichuan University. The protocol has received approval from the Biological and Medical Ethics Committee of West China Hospital (2016 Reviewed-No. 331). This protocol is also registered in the Chinese Clinical Trial Registry (ChiCTR-IOR-17010675). The written informed consent is obtained from each participant or their legal surrogate after fully informed.

**Figure 1 F1:**
[figure not shown]
Flow chart of the clinical trial. CTA = CT angiography, NCCT = noncontrast CT, SBP = systolic blood pressure, sICH = spontaneous intracerebral hemorrhage.

### Study objective

2.2

The key primary objective is to compare the relative reduction of peri-hematoma rCBF in sICH patients with cerebrovascular stenosis under different BP treatments and discuss whether the degree of stenosis or location of stenosis on relative main arteries has an effect on the peri-hematoma rCBF by analysis of subgroups. The other primary objectives are to analyze the absolute change of cerebral perfusion indexes, the occurrence rate of ischemic stroke, and incidence of hematoma expansion within 7 days. The key second objective is to determine the effects of different BP managements on unfavorable clinical outcome at 90-day in sICH patients with cerebrovascular stenosis. The other secondary objectives are to assess the effects of the treatments separately on death and dependency through physical function, health-related quality of life, other vascular events, and hospital stays.

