### Sample size

2.4

The initial assessment of sample size is based on taking peri-hematoma rCBF as the ischemic reign of brain tissue.^[14]^ For no study now available referring to the field, the pilot trial was conducted to assess the sample size.

The pilot data includes 12 patients (6/each group) and shows the rate of reduction of peri-hematoma rCBF are (0.4282 ± 0.14705) and (0.3555 ± 0.12592) in intensive/conservative BP-lowering group, compared with that of contralateral homologous reign. For the reduction of relative rCBF, ≥44%^[28]^ is regarded as a threshold of infarction, if the difference of 2 groups is more than 9% (9%+35.5%>44%); acute SBP lowering is considered to significantly increase the risk of infarction in these patients. So, each sample size of 36 in a group will be required to detect a significant difference of 5% (2-tailed) and a power of 90% (PASS software Version 11.0.4; NCSS). In view of 10% patients lost to follow-up, a total of 80 patients (40 in each group) will be included in this trial.

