### Statistical analysis

2.9

The analysis of this study is based on the intention-to-treat principle. The continuous variable of primary outcome and second outcomes will be assessed by *t* test. The Chi-square test will be used to assess the categorical data of second outcomes. Log-rank test will be used to analyze the time-to-event type of outcomes. Subgroup analysis will be conducted by level of cerebrovascular stenosis and location of the cerebrovascular stenosis.

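### The key primary objective asks whether stenosis degree or location affects peri-hematoma rCBF, but the stated analysis names no test of a stenosis term or of a treatment-by-stenosis interaction

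*Protocol article*

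**What the plan says.** The key primary objective in section 2.2 has two parts. The first compares relative rCBF reduction between the BP strategies. The second is to "discuss whether the degree of stenosis or location of stenosis on relative main arteries has an effect on the peri-hematoma rCBF by analysis of subgroups".

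Section 2.9 covers the method in two separate sentences: "The continuous variable of primary outcome and second outcomes will be assessed by *t* test", and later "Subgroup analysis will be conducted by level of cerebrovascular stenosis and location of the cerebrovascular stenosis". It gives no regression model, no comparison of one stenosis class with another, and no interaction test.

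Three other places bear on the point. Section 2.5 uses the same two factors, level and location, in the minimization. Section 2.7.5 divides location into anterior and posterior circulation. Section 2.4 sizes the trial on the comparison of BP arms alone.

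**The concern.** The stenosis question can be read in two ways. One null is that mean rCBF reduction is the same in each stenosis class (a main effect of stenosis). The other is that the difference between BP arms is the same in each class (an interaction). An arm-versus-arm t test inside one class has a third null: no treatment difference in that class. It never compares one class with another.

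If the stenosis conclusion is drawn by setting such tests side by side, a result that is significant in one class and not in the other will look like a stenosis effect. In classes of about 20 per arm, chance alone often produces that pattern. Conversely, if stenosis shifts rCBF equally in both arms, the shift cancels out of every within-class comparison and cannot be seen. Part of the key primary objective would then rest on a contrast that does not address it.

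**Working it through.** **Inputs from the protocol article**
- Section 2.4: planning difference 0.09; pilot SDs 0.14705 (intensive) and 0.12592 (conservative); two-sided 5%; 90% power; 36 per group, or 40 after 10% loss.
- Pilot difference: 0.4282 − 0.3555 = 0.0727.
- Pooled SD: √[(0.14705² + 0.12592²)/2] = 0.1369.

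**Assumptions.** Each factor has two classes (the article gives two for location and no cut-point for level). Class shares are not given; splits from 50:50 to 80:20 are used.

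**The plan's own figure.** n = 2(1.960 + 1.282)² × 0.1369² / 0.09² gives 49 per group (50 with the t distribution), not 36. At 36 per group, power is 79.7% (normal) or 78.6% (t). The loss step reproduces: 36/0.9 = 40. The 36-versus-90% mismatch is a separate matter. The range below includes a difference of 0.1046 (about 0.105), at which 36 per group does give 90% power.

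**Same treatment effect in both classes.** Let p and q be the power of the t test in each class. Exactly one test is significant with probability p(1 − q) + q(1 − p).

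With 36 per arm split evenly (18 per arm per class) and a difference of 0.09, the noncentrality is 0.09 / (0.1369 × √(2/18)) = 1.97. So p = q = 0.483, and 2 × 0.483 × 0.517 = 49.9% (simulated: 49.4%).

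| Per arm | Split | Diff. 0.0727 | Diff. 0.09 | Diff. 0.1046 |
|---|---|---|---|---|
| 36 | 50:50 | 44.9% | 49.9% | 47.8% |
| 36 | 70:30 | 47.3% | 54.7% | 55.1% |
| 36 | 80:20 | 50.8% | 61.3% | 65.1% |
| 40 | 50:50 | 46.8% | 49.9% | 45.3% |
| 40 | 70:30 | 49.8% | 55.7% | 54.1% |
| 40 | 80:20 | 53.5% | 62.6% | 64.4% |

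The range is 45% to 65% per factor. With even splits and a difference of 0.09, at least one of the two factors shows the pattern in about 66% of simulated trials. An interaction test rejects in 4.7% (36 per arm) or 5.3% (40 per arm).

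**No treatment effect.** 2 × 0.05 × 0.95 = 9.5% per factor; simulated 16% for either factor.

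**True stenosis main effect of 0.09 (36 per arm, even split).** The one-significant-one-not rate barely moves: 50.2% against 49.4% with a treatment effect, and 10.1% against 9.4% without. A direct test of the stenosis class has standard error 0.1369 × √(2/36) = 0.0323 and detects the effect in about 78% to 79% of trials. At 40 per arm the figure is 83% (50:50) or 76% (70:30).

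**True interaction of 0.09.** With 18 per cell the standard error is 0.1369 × √(4/18) = 0.0645. Power is about 28%, and the 95% CI half-width is about 1.995 × 0.0645 = 0.13. Across 36 to 40 per arm and the 50:50 and 70:30 splits simulated, power is about 26% to 31%.

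**The case against.** The strongest reply is that the criticised analysis is not written down. The t test and the subgroup analysis stand in separate sentences of section 2.9. Neither says that arms are compared within classes or that p values are then contrasted. A t test between stenosis classes, for example anterior against posterior, is not excluded; it would address the literal wording of section 2.2 with 5% error. Subgroup means and CIs would also allow the class differences to be compared directly. The article is condensed, the exact subgroup test may be in a document not shown, and section 2.2 only says that the matter will be discussed.

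Much of this stands. A reader might infer that within-class t tests are the only planned method, that contrasting p values is the only possible route to a conclusion, or that about half of all such trials would report a false stenosis effect. The documents support none of these as stated. The first is an inference from two adjacent sentences, and the second is wrong. The third needs a real, uniform treatment effect near the planned size and someone who reads discordant p values as a stenosis effect. Nor does any section propose BP targets by stenosis class.

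What does not fall is the mismatch. Section 2.2 does not leave the route open: it ties a key primary question to subgroup analysis, and the only test named for that outcome does not, on its natural reading, address the question. Two analysts following the text could reach opposite stenosis conclusions.

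**Conclusion.** The point holds in conditional form. The stenosis question belongs to the key primary objective, and no stated test targets either a stenosis term or a treatment-by-stenosis interaction.

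If BP arms are compared within classes and the results contrasted, a uniform treatment effect near 0.09 yields a misleading split in about 45% to 65% of trials per factor, against 5% for an interaction test. A stenosis main effect stays invisible. With no treatment effect the rate is about 10%. These figures rest on the pilot SDs, normal outcomes, two classes per factor, assumed class shares and true differences of 0.073 to 0.105. The overall comparison of BP arms is not affected.

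**What to change.** In section 2.9, specify for this objective:
1. One linear model of relative rCBF reduction on arm, stenosis level and stenosis location, the minimization factors. Answer the stenosis question from the level and location terms.
2. A second step that adds arm × level and arm × location, reported as exploratory estimates with 95% CIs.
3. Within-class treatment differences shown as estimates with CIs only, with a sentence that significance in one class and not in another is not evidence of a stenosis effect.

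In section 2.2, separate the two readings of the stenosis question and label the interaction part exploratory.

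The cost is wording and a regression on data already collected; no patients or procedures are added. The downside is wide interaction CIs: with power of about 26% to 31% for an interaction as large as the planned treatment difference, a real interaction will often be missed and its absence cannot be concluded.

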### Patients population

2.3

#### Inclusion criteria

2.3.1

(1)Age ≥18 years;(2)Randomized to groups within 6 hours from onset;(3)Acute spontaneous ICH, verified by noncontrast CT (NCCT) or magnetic resonance imaging;(4)Cerebrovascular luminal narrowing (30–70%) demonstrated with CT angiography (CTA) upon admission;(5)SBP is from 150 to 220 mm Hg (twice repeat measurements, record ≥2 minutes apart)

#### Exclusion criteria

2.3.2

(1)Known definite contraindication to intensive BP-lowering treatment (e.g., severe cerebrovascular stenosis (>70%), severe aortic valve stenosis, severe renal failure);(2)Known definite indication to intensive BP-lowering treatment (e.g., very high SBP ≥220 mm Hg; hypertensive encephalopathy; aortic dissection);(3)The ICH is caused by secondary factors (e.g., intracranial aneurysm; arteriovenous malformation; tumor stroke; anticoagulant correlation hemorrhage).(4)Glass coma scale ≤5 or deep coma;(5)Disabled or with underlying diseases (e.g., known dementia, severe cardiovascular disease, kidney failure) before onset;(6)History of ischemic stroke within 30 days before onset of sICH;(7)Known indication of emergency surgery (volume of supratentorial hematoma ≥30 mL or volume of infratentorial hematoma ≥10 mL; within 48 hours from onset; Glass coma scale ≥5);(8)Contraindication to CT perfusion imaging (CTP) (e.g., contrast allergy, pregnancy, or creatinine ≥160 mmol/L).

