#### Imaging procedures

2.7.3

A standard NCCT and CTA are conducted when admitted in emergency department, by a 64-slice CT scanner (SOMATOM Definition Flash; Siemens Healthcare Sector, Forchheim, Germany). The scanning parameters of NCCT are 120 kVp, 340 mA, and 5 mm slice thickness. The hematoma volume is calculated by the ABC/2 method.^[30]^ CTA is initiated after the infusion of 100-mL contrast material (80 kVp, 110 mA, 1 mm slice thickness, and pitch 1:1). 3D reconstructions of CTA are performed to assess the level of cerebrovascular stenosis. NCCT (120 kVp, 340 mA, and 5 mm slice thickness) and CTP are conducted 24 ± 3 hours after randomization in order to assess for additional HE and perihaematoma rCBF with different treatments. The CTP will be initialed after the infusion of 42 mL contrast material given over 12 seconds with CT images acquired every 1.5 seconds at most 50 seconds (70 kVp, 150 mA, 1 mm slice thickness).

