#### Image analysis: CTA and CT perfusion

2.7.5

The stenosis is defined as the reduction of an artery diameter ≥50%^[31–33]^ or occlusion with digital subtraction angiography (DSA), magnetic resonance angiography, or CTA, and severe is defined as ≥70%.^[34]^ The cut-off values on CTA should be 30% to detect all lesions ≥50% on DSA, by which the CTA has a similar high sensitivity and specificity for detecting the stenosis of large cerebral vessels.^[35]^ The stenosis is detected by 3D image of CTA, and then the level of stenosis is calculated by the 2D gray scale MPR images with window and level of 1000 and 500 HU (Fig. 2), respectively.^[36]^ AHA/American Stroke Association guidelines^[29]^ suggest that severe cerebrovascular stenosis is a contraindication for intensive treatment. The included patients are divided into groups according the location of stenosis, such as anterior circulation (internal carotid artery, anterior cerebral artery, middle cerebral artery, posterior cerebral artery) and posterior circulation (vertebral artery or basilar artery and others lesions). Raw contrast-enhanced CT images are analyzed by a technician and are checked by a senior technician to ensure the accuracy. The perhematoma region is defined as the region of 1 cm from the margin of hematoma, excluding subarachnoid and intraventricular space.^[37]^ The vessels are also removed from the region, which show as voxel with CBF >100 mL/100 g/min or 8 mL/100 g.^[38–40]^ The mean rCBF, Tmax, MTT, and rCBV of perhematoma region and contralateral homologous regions are calculated with removal of vessels. In addition, the mean rCBF, Tmax, MTT, and rCBV of hemisphere are also used to analyze the difference in 2 treatments. Hypoperfusion is defined as absolute CBF <18 mL/100 g/min, or delay of MTT and Tmax more than 2 seconds, and severe hypoperfusion is CBF <12 mL/100 g/min.^[41,42]^ Relative rCBF, Tmax, MTT, and rCBV are defined the ratio of parameters of perhematoma region to those of contralateral homologous regions (Fig. 2).

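### Two eligibility limits are wrong as written: creatinine is in mmol/L instead of µmol/L, and a stenosis of exactly 70% is eligible although the protocol classes it as severe

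*Protocol article*

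**What the plan says.** **Renal limit.** Section 2.3.2, exclusion (8), bars patients who have a contraindication to CT perfusion imaging and gives as examples "contrast allergy, pregnancy, or creatinine ≥160 mmol/L". Kidney function appears in two other exclusions, neither with a number. Exclusion (1), on contraindications to intensive lowering, lists "severe cerebrovascular stenosis (>70%), severe aortic valve stenosis, severe renal failure". Exclusion (5), on pre-existing disability or disease, lists "known dementia, severe cardiovascular disease, kidney failure".

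**Contrast load.** Section 2.7.3 describes two contrast examinations. At admission, "CTA is initiated after the infusion of 100-mL contrast material". At 24 ± 3 hours after randomisation, CT perfusion starts "after the infusion of 42 mL contrast material given over 12 seconds". The second scan supplies the key primary outcome (section 2.7.4).

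**Stenosis limits.** Inclusion (4) in section 2.3.1 requires "Cerebrovascular luminal narrowing (30–70%) demonstrated with CT angiography (CTA) upon admission". Exclusion (1), quoted above, sets the severe category at >70%. Section 2.7.5 sets it differently: "severe is defined as ≥70" per cent, with CTA among the modalities named. The same section says that guidelines "suggest that severe cerebrovascular stenosis is a contraindication for intensive treatment".

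**The concern.** Both items are numbers that a screener applies to decide whether a patient may safely enter the trial.

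The creatinine limit is meant to keep patients with impaired kidneys from a contrast dose that the trial itself requires. If the printed value can never be reached, that check does nothing. A patient above the evidently intended limit but short of renal failure is then left to the clinician's judgement.

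The stenosis limits use one word, severe, with two definitions. At the boundary they disagree about whether a patient belongs in the trial. The trial's own rationale (section 1) is that intensive lowering may cause ischaemia where arteries are narrowed, so the upper stenosis limit is a central safety limit. As written, a patient read at 70% can be randomised to a treatment that section 2.7.5 reports as contraindicated for that degree of narrowing.

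**Working it through.** No sample size, power or significance level enters here, so there is no design figure to reproduce. The check is a unit conversion and a boundary test.

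**1. Creatinine**

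Inputs: the printed limit of 160 mmol/L (section 2.3.2, exclusion 8), and the molar mass of creatinine, 113.12 g/mol. The molar mass is a chemical constant that the article does not give.

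- As printed: 160 mmol/L × 113.12 mg/mmol = 18,099 mg/L, or 18.1 g/L, or about 1,810 mg/dL.
- With µmol/L: 160 µmol/L × 0.11312 mg/µmol = 18.1 mg/L, or about 1.81 mg/dL.
- Ratio: 160 mmol/L = 160,000 µmol/L, and 160,000 / 160 = 1,000.

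The printed limit is physiologically impossible. The same number in µmol/L is a plausible renal cut-off for contrast.

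**2. Contrast that the limit governs**

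Inputs: 100 mL at CTA and 42 mL at CT perfusion (section 2.7.3).

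- Total: 100 + 42 = 142 mL.
- Share given at CT perfusion: 42 / 142 = 30%.

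Eligibility already requires the CTA, so exclusion (8) controls only the later 42 mL. That dose comes on top of the first one.

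**3. Stenosis boundary test**

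Rules: eligible if 30 ≤ s ≤ 70 (section 2.3.1); excluded by the stated limit if s > 70 (section 2.3.2); severe if s ≥ 70 (section 2.7.5).

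| CTA reading | Meets inclusion (4) | Caught by >70% | Severe in 2.7.5 | Consistent |
|---|---|---|---|---|
| 30% | yes | no | no | yes |
| 50% | yes | no | no | yes |
| 69% | yes | no | no | yes |
| **70%** | **yes** | **no** | **yes** | **no** |
| 71% | no | yes | yes | yes |

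The conflict sits at one value only.

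**4. Chance of the intensive arm at 70%**

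Input: 40 of 80 patients planned per group (section 2.4). 40 / 80 = 1/2.

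**5. After correction**

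With µmol/L the renal limit becomes about 1.81 mg/dL. With inclusion at 30 ≤ s < 70 and exclusion at s ≥ 70, a 70% reading is not eligible, is excluded and is severe, so all three sections agree. The planned sample size does not change.

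**The case against.** The strongest reply is that these are two wording slips in a condensed article, not faults of design.

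On creatinine: the value is so plainly impossible that any clinician would read it as µmol/L. It is only an example, and the governing rule, a contraindication to CT perfusion, stands without it. Renal failure is excluded twice elsewhere. The full protocol may carry the right unit, and the letter could even have been changed in production of the article. Most of this stands. It makes the practical effect smaller than a factor of 1,000 suggests. It does not make the printed limit work, and the other two renal exclusions have no threshold and are worded for failure, not moderate impairment.

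On stenosis: the >70% figure is also an example under a wider exclusion of any known definite contraindication to intensive lowering. A careful reader who joins that clause to section 2.7.5 would exclude a 70% reading, and exclusions override inclusions. Section 2.7.5 also reports guidelines as suggesting the contraindication and does not issue its own rule. This is a fair reading, but it needs the screener to set aside the explicit number in the eligibility list in favour of a definition in the imaging section. Exclusion (1) itself lists severe stenosis as a definite contraindication, so the protocol does adopt the principle; only the cut-off differs.

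A third reply is that section 2.7.5 mixes scales, using 30% on CTA to capture 50% on digital subtraction angiography. That adjustment is given for the lower limit only. The definition of severe names CTA and offers no separate upper limit for it, so the scale difference does not remove the conflict.

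**Conclusion.** Both limits are wrong as written and should be corrected.

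- **Creatinine:** the unit is wrong by a factor of 1,000, and the only numeric renal limit in the article excludes nobody. This rests on reading 160 µmol/L as the intended value, which the number itself strongly suggests. The effect is bounded, because the rest of exclusion (8) and the two unnumbered renal exclusions still apply.
- **Stenosis:** a reading of exactly 70% is admitted by inclusion (4), missed by the limit in exclusion (1) and severe in section 2.7.5. Neighbouring readings are handled consistently. The article gives no basis for saying how many patients this concerns; each would have about a 1 in 2 chance of intensive lowering.

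The consequence is for patient safety and consistent screening. The endpoint, power and planned analysis are not affected.

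**What to change.** 1. In exclusion (8), replace mmol/L by µmol/L. Check the full protocol and the screening form for the same unit.
2. In inclusion (4), set the CTA range to 30% to <70%.
3. In exclusion (1), set severe cerebrovascular stenosis to ≥70%, so that it matches section 2.7.5.

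If the full protocol carries these errors, the cost is a short amendment with one unit and two limits changed, approved by the ethics committee before use (section 2.12). If any of them is in the article alone, a correction to the article is enough for that item. Patients read at exactly 70% become ineligible; nothing else in the design moves.

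One similar overlap can be tidied at the same time: an SBP of exactly 220 mm Hg falls inside the range of inclusion (5) and is also excluded by exclusion (2), which starts at 220.
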